# Clinical study on concurrent use of electro-acupuncture or Chuna manual therapy with pregabalin for chemotherapy-induced peripheral neuropathy: safety and effectiveness (open-labeled, parallel, randomized controlled trial, assessor-blinded)

**DOI:** 10.1097/MD.0000000000018830

**Published:** 2020-01-17

**Keywords:** acupuncture, chemotherapy-induced peripheral neuropathy, electroacupuncture, manual medicine, pregabalin

## Abstract

**Introduction::**

Chemotherapy-induced peripheral neuropathy (CIPN) is one of the major side effects of chemotherapy. Its main symptoms are pain, paresthesia, and numbness. However, the mechanisms underlying the development of CIPN remain unclear and standard treatments have not been established. Recently, there has been a growing interest in various approaches to overcome the limitations of the existing treatments. This study aims to evaluate the efficacy and safety of the concurrent use of two complementary and alternative therapies: electroacupuncture (EA) and Chuna manual therapy (CMT), with pregabalin, which is the conventional pharmacotherapy for neuropathic pain.

**Methods/design::**

This is an open-label, parallel, assessor-blinded randomized controlled trial, which includes 90 patients with colorectal and breast cancer, who developed CIPN. After a 2-week preparation period, the patients are divided into three groups (pregabalin administration group, pregabalin + EA treatment group, and pregabalin + CMT treatment group), treated for approximately 5 weeks and followed-up 4 weeks after treatment. The primary outcome is assessed using the Functional Assessment of Cancer Therapy/Gynecologic Oncology Group Neurotoxicity subscale score (version 4.0) and the secondary outcome is measured using the Quality of Life Questionnaire-CIPN 20-Item Scale (version 3.0) and the quality of life questionnaire (version 3.0) developed by the European Organisation for Research and Treatment of Cancer. Moreover, exploratory efficacy and safety evaluations will be conducted based on the chemotherapy-completion rate and nerve conduction studies.

## Introduction

1

Chemotherapy-induced peripheral neuropathy (CIPN) is a significantly common adverse effect of anticancer drug, with high prevalence. Approximately 68% of patients receiving chemotherapy develop symptoms of CIPN within 1 month,^[1]^ which include neuropathic pain, numbness, burning, and tingling of the skin. These symptoms may last for a long time, resulting in a rapid deterioration in the quality of life.^[2–4]^

Several anticancer agents can induce CIPN, including platinum analogs (cisplatin, carboplatin, and oxaliplatin), antitubulins (paclitaxel, docetaxel, ixabepilone, vincristine), proteasome inhibitors (bortezomib), and others (thalidomide); however, the mechanisms underlying this drug-induced neurotoxicity remain unclear, and genetic risk factors, past medical history, and association with other drugs are also known to be closely related to the occurrence of CIPN.^[5,6]^ Due to these limitations, there is no standardized treatment protocol for CIPN. In general, various drugs that are effective for neuropathic pain, such as nerve-protective agents, ion channel targeted agents, antioxidants, and anti-inflammatory agents are used for the treatment of CIPN, based on the clinician's preference and the patient's symptoms; however, the evidence of their efficacy for treating CIPN is insufficient, except duloxetine.^[7–9]^ Moreover, these drugs may also be less effective and causes adverse effects such as dizziness, weight gain, somnolence, peripheral edema, and fatigue.^[10,11]^

Recently, various studies have reported the treatment of CIPN with complementary and alternative medicine (CAM).^[12,13]^ Acupuncture (including electroacupuncture [EA]) is the most popular CAM therapy and is reportedly effective for treating cancer-related symptoms, such as CIPN, aromatase inhibitor-associated arthralgia, and post-neck dissection pain.^[14]^ Moreover, some articles on herbal medicine, manual medicine and exercises reported positive effects on several peripheral neuropathy, including CIPN.^[15,16]^ However, research has focused only on the efficacy of each CAM intervention for CIPN, and there are very few studies on its efficacy combined with conventional treatment.

The present study aims to verify the safety and efficacy of the concurrent use of EA or Chuna manual therapy (CMT) (a manual medicine treatment widely used in Korea) with pregabalin for patients with CIPN (especially, taxane-induced peripheral neuropathy in breast cancer and oxaliplatin-induced peripheral neuropathy in colorectal cancer), compared to pregabalin therapy alone. We hope that this study will validate the efficacy and safety of combination therapy and suggest a new approach for the treatment of CIPN.

## Objective

2

The study aims to verify the hypothesis that the concurrent use of CMT or acupuncture treatment with pregabalin, a medication commonly used for CIPN is more effective and safe for the relief of CIPN symptoms than is pregabalin-alone therapy.

## Methods

3

### Trial registration

3.1

This study has been registered in the Clinical Research Information Service (CRIS; trial registration number: KCT0004217; trial protocol version: IS18ENSI0054 version 2.0; https://cris.nih.go.kr/cris/en/search/search_result_st01.jsp?seq=12752).

### Study design

3.2

This study is designed as an open-label, parallel, assessor-blinded randomized controlled trial. This study will be conducted at the Catholic Kwandong University International St. Mary's Hospital, Incheon, South Korea. The diagrammatic representation of this study is presented in Figure 1. The patients will receive a full explanation of the details of the trial from investigators. Through this procedure, if they agree to participate in the trial, a signed consent form will be obtained.

**Figure 1 F1:**
[figure not shown]
Flow chart of the trial. CMT = Chuna manual therapy, EA = electroacupuncture.

The patients visit the hospital five times for evaluation. Screening (visit 1) includes only those participants who have submitted the informed consent form. For screening, demographic information, medical history, physical examination, vital sign, questionnaire survey, laboratory test, pregnancy test (childbearing age females), neurological exam (decided by the attending physician for exclusion diagnosis purpose), and selection/exclusion criteria were be evaluated. Patients who have passed the screening test will have a 7-day run-in period, during which all medications prescribed for controlling the symptoms of peripheral neuropathy will be stopped.

Ninety patients were enrolled and randomly divided into three groups. However, if no such drugs were being used during the screening test, randomization began immediately. The visits are designed for patient evaluation at approximately 2 weeks (visit 2: baseline visit), 4 weeks (visit 3), 7 weeks (visit 4), and 11 weeks (visit 5: outpatient follow up) after the screening test. These visits include evaluation of the medical and medication history, basic physical examination, vital signs, laboratory tests, pregnancy test (for women of childbearing age), primary effectiveness and secondary effectiveness assessments, exploratory effectiveness assessment (chemotherapy completion rate: whether all planned chemotherapy procedures were performed without interruption due to CIPN), and nerve conduction study (NCS). The coordinators of the trial will inform the patient of the next visit schedule for each visit and encourage participation. The clinical trial conductor will instruct the participant to ensure compliance with the treatment. The assessment of treatment compliance with pregabalin will be based on the planned dose and the actual dose taken, as well as the quantity returned and the quantity not returned at each patient visit. The calculation is based on the actual number of treatments compared to the planned number of treatments for EA and CMT.

Only those patients who have completed the informed consent form with full acceptance of the expected effects and predicted adverse reactions to clinical trial interventions prior to commencement of the study may participate in the study. In the event of an accident or adverse event, appropriate measures will be taken according to the investigator's judgment and the participant will be compensated. Moreover, the study will be conducted ethically, in compliance with the principles of the Good Clinical Practice (GCP) guidelines and the revised version of the Declaration of Helsinki.

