#### Pregabalin (usual care) group

3.4.1

Pregabalin is known to have positive effects on several symptoms of neuropathic pain, including CIPN.^[11]^ Pregabalin group with repeated oral administration of one capsule of pregabalin (Product name, Lyrica capsule, 75 mg) 30 min after meals twice a day after the screening test. If the participant is already taking more than 150 mg/day of pregabalin, the dose will be maintained without reduction (≤600 mg/day).

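### Patients on no neuropathy drugs are randomised at screening but have their baseline visit about 2 weeks later, so the self-reported baseline can follow open allocation

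*Protocol article*

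**What the plan says.** Four places in the protocol article bear on the order of events.

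- **Abstract, Methods/design:** "After a 2-week preparation period, the patients are divided into three groups", who are then "treated for approximately 5 weeks and followed-up 4 weeks after treatment".
- **Section 3.2, run-in:** those who pass screening enter a run-in of 7 days, "during which all medications prescribed for controlling the symptoms of peripheral neuropathy will be stopped".
- **Section 3.2, exception and visits:** "However, if no such drugs were being used during the screening test, randomization began immediately". The next sentence reads "The visits are designed for patient evaluation at approximately 2 weeks (visit 2: baseline visit", followed by visits at about 4, 7 and 11 weeks, all counted from screening. It makes no exception for patients randomised at once.
- **Section 3.4.1:** pregabalin is taken "30 min after meals twice a day after the screening test", and "If the participant is already taking more than 150 mg/day of pregabalin, the dose will be maintained without reduction", up to a stated ceiling.

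Three further statements matter. The primary outcome is the change in FACT/GOG-Ntx from baseline, completed by the participant (section 3.8.1). It is compared between arms by ANOVA on the change at the end of week 5 (section 3.9). Participants cannot be blinded (section 3.6).

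**The concern.** A baseline is protected from bias because it is recorded before anyone knows the allocation. The exception in section 3.2 removes that protection for patients who take no neuropathy drugs at screening. They are allocated at about week 0, while the visit labelled as baseline falls at about week 2. A participant who knows that electroacupuncture or Chuna has been added, or that it has not, may rate symptoms differently. Blinding the assessor does not help, because the participant supplies the score.

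The planned ANOVA on change subtracts this baseline directly. Any difference between arms in baseline reporting that is caused by knowing the arm therefore passes into the treatment contrast.

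A second, separate conflict concerns what baseline measures. A patient taking pregabalin for neuropathy above the stated dose is told in section 3.2 to stop and in section 3.4.1 to continue. Depending on which passage a site follows, that baseline is a washed-out value or an on-drug value.

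**Working it through.** **1. Visit weeks.** Inputs: screening at week 0 and visits at weeks 2, 4, 7 and 11 (section 3.2); preparation of 2 weeks, treatment of about 5 weeks and follow-up of 4 weeks (abstract).

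- Preparation: 2 − 0 = 2 weeks
- Treatment: 7 − 2 = 5 weeks
- Follow-up: 11 − 7 = 4 weeks

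The visit schedule reproduces the abstract. The intended scheme appears to be treatment from visit 2 to visit 4.

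**2. Allocation against baseline.**

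| Source | Allocation | Baseline visit | Allocation to baseline |
|---|---|---|---|
| Abstract, with section 3.2 visit times | after 2-week preparation | week 2 | about 0 weeks |
| Section 3.2, no neuropathy drugs at screening | at once, about week 0 | week 2 | about 2 weeks |

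The two rows cannot both describe the same patient.

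**3. How a shift enters the result.** Let *d* be the difference between two arms in the mean baseline shift caused by knowing the arm, among patients randomised immediately, and let *p* be their share of each arm. The between-arm difference in mean change moves by *p* × *d* in absolute value. Its direction is not determined: expectation may raise or lower reported symptoms.

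**4. Size, under assumptions.** The subscale has 11 items scored 0 to 4 (section 3.8.1), so its range is 11 × 4 = 44 points. The document gives no SD, no expected shift and no value for *p*. Assume *d* = 1 to 2 points and an SD of change of 5 to 8 points.

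- Smallest: 1 / 8 = 0.125 SD
- Largest: 2 / 5 = 0.40 SD

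| Assumed share *p* | Bias in SD units |
|---|---|
| 25% | 0.03 to 0.10 |
| 50% | 0.06 to 0.20 |
| 75% | 0.09 to 0.30 |
| 100% | 0.13 to 0.40 |

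**5. Run-in against dose maintenance.** Section 3.2 stops every medication prescribed for neuropathy symptoms. Section 3.4.1 keeps existing pregabalin above 150 mg/day. For a patient taking it for chemotherapy-induced neuropathy, both cannot apply during the run-in. All three arms receive pregabalin on the same terms (sections 3.4.1 to 3.4.3), and this status is fixed before randomisation. The mix of baselines is therefore balanced between arms in expectation. It adds variability to the change score rather than a systematic difference.

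**The case against.** The strongest reply is that the sponsor means the run-in to be waived and visit 2 brought forward for patients who need no washout. Visit times are approximate, so this is possible. Screening also includes an unnamed questionnaire survey, so a score from before allocation may exist. No passage says exactly when a participant learns the arm. Figure 1 is not available, and the article condenses a fuller protocol that may hold a detailed schedule. These points limit the finding to what the text allows, and they do not show that every site does it. But none of them is written down, and they do not remove a conflict between sentences in the same paragraph.

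A reader might infer more than the documents support:

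- **That treatment starts before baseline.** The pregabalin wording in section 3.4.1 sets only an earliest time and does not show that dosing precedes visit 2. No passage starts electroacupuncture or Chuna before visit 2, and the 2/5/4-week arithmetic suggests that they begin there.
- **That 7 days and 2 weeks contradict each other.** A 7-day run-in can fit inside a 2-week preparation period.
- **That early or continued pregabalin biases the comparison.** It is common to all arms. It would mainly dilute change or add noise.
- **That the whole shift reaches the treatment effect.** It does so only in proportion to the share of patients randomised immediately, which is not stated.

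**Conclusion.** The point holds as an inconsistency that can bias the primary comparison. As written, section 3.2 permits a self-reported baseline about 2 weeks after open allocation in patients on no neuropathy drugs, against the order in the abstract. The possible bias is 0.13 to 0.40 SD times the share of such patients, or about 0.06 to 0.20 SD if half are affected. The shift, the SD and the share are all assumptions, so these figures illustrate scale and do not estimate the bias. The planned ANOVA on change cannot remove a shift of this kind, which is why the order should be settled before patients are randomised.

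The conflict between stopping and maintaining pregabalin is real but lesser. It leaves baseline without one meaning and mainly costs precision.

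**What to change.** Define baseline for every patient as the FACT/GOG-Ntx, QLQ-CIPN20 and QLQ-C30 assessment completed before allocation is released. State in section 3.2 that these questionnaires come ahead of randomisation, including in patients who need no washout, and make the abstract agree.

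Reconcile the run-in, pregabalin-maintenance and pregabalin-start passages (sections 3.2 and 3.4.1) with each other and with the visit schedule. Which clinical rule applies is for the investigators to decide.

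The cost is a short amendment and no extra visits. In patients on no neuropathy drugs, either the baseline questionnaires are brought forward or randomisation is delayed by up to about 2 weeks. If the questionnaires are brought forward to screening while visit 4 stays at week 7, the baseline-to-endpoint interval becomes 7 − 0 = 7 weeks for these patients, against 5 for the others. The amendment should therefore also state the point from which visit weeks are counted.

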### Sample size calculation

3.3

This study is a pilot clinical trial, which aims to evaluate the efficacy and safety of combined treatment with EA and CMT, compared to the conventional-therapy group (pregabalin treatment group). We determined that it would be desirable to proceed with the minimum number of participants possible, to meet the goals of this study. Moreover, earlier clinical studies involving acupuncture or EA for CIPN have included sample sizes of about 20 participants per group.^[17,18]^ Thus, we concluded that this study should include 30 participants in each group (total sample size: 90). Even if the dropout rate is assumed to be 20%, this sample size is larger than that for similar earlier studies.

### Intervention

3.4

#### Pregabalin (usual care) group

3.4.1

Pregabalin is known to have positive effects on several symptoms of neuropathic pain, including CIPN.^[11]^ Pregabalin group with repeated oral administration of one capsule of pregabalin (Product name, Lyrica capsule, 75 mg) 30 min after meals twice a day after the screening test. If the participant is already taking more than 150 mg/day of pregabalin, the dose will be maintained without reduction (≤600 mg/day).

#### Electroacupuncture treatment group

3.4.2

The EA-treatment group is to be treated with EA, in addition to the treatment for the conventional-therapy group. A disposable sterilized needle made of stainless steel (0.2 mm ∗ 30 mm, Spring Handle Needle, DONGBANG Medical Co, LTD) will be used for treatment, and the EA device is STN-330 (Maximum Output Frequency: 240 Hz, Maximum Output Current-Low 7.3 mA, High 13.0 mA, Stratek. Co. LTD). The acupuncture points to be used for treatment are: ST 40, GB 34, EX-LE 10, EX-UE 11, TE 5, LI 4, ST 36, KI 6, CV 4. Of them, ST 40 and GB 34, TE 5; LI 4, ST 36, and KI 6 are paired with each other and a 20-min long electrical stimulation is applied with a 2-Hz mixed pulse, while EX-LE 10, EX-UE 11, and CV4 are not electrically stimulated. The final acupoints were selected through network analysis for the EA treatment. The EA treatment is conducted three times per week for the first 2 weeks and then twice per week for the following 3 weeks.

#### Chuna manual therapy group

3.4.3

The CMT group is treated with CMT, in addition to conventional therapy. In Chuna treatment, patients with colorectal cancer lie down on their side and Sunwoo manual therapy, which helps joint movement and improves overall function is used.^[19]^ Sunwoo manual therapy may cause unnecessary irritation to the area affected by breast cancer. Thus, CMT for meridian sinew system, which is applied to the nerves of the ribs, upper and lower limbs is utilized. CMT is conducted twice a week for the first 2 weeks and once a week for the following 3 weeks.

### Inclusion and exclusion criteria

3.5

#### Inclusion criteria

3.5.1

The inclusion criteria as follows:

1.adult men and women aged 18 to 85 years;2.patients with colorectal cancer with oxaliplatin-induced peripheral neuropathy or patients with breast cancer patients with taxane-induced with peripheral neuropathy (provided that the patients have had peripheral neuropathy for 1 month or longer after the chemotherapy before the time of screening and have peripheral grade 2 or higher sensory/motor neuropathy, based on the Common Terminology Criteria for Adverse Events (CTCAE) V5.0 at the time of screening);3.those who do not have significant restrictions on their behavior and life, corresponding to Eastern Cooperative Oncology Group (ECOG) 0–2;4.patients who can read the symptom questionnaire, comprehend it, and answer accordingly;5.patients who have given their consent for the clinical protocol and follow-up and in the Institutional Review Board (IRB)-approved document.

#### Exclusion criteria

3.5.2

The following patients would be excluded from participating in the trial:

1.patients with neuropathy, caused by factors besides chemotherapy (diabetes, peripheral vascular disease, alcohol-induced neuropathy, drug-induced neuropathy, and other neurological disorders);2.patients with a history of renal disease or with a medical history that contraindicates the use of pregabalin, according to the treating physician;3.patients with conditions that affect the progress of Korean medicine treatments (EA, CMT) such as skin lesion or fractures;4.patient with fear or aversion toward Korean medicine (EA therapy, CMT);5.patients who received oriental medical treatment such as acupuncture, moxibustion, cupping therapy, and oriental medication for CIPN, within 1 week of screening;6.patients with other diseases or factors that may be regarded as inappropriate for the clinical study;7.if the treating physician has determined that the patient is unsuitable for participation in this study;8.women of childbearing age and pregnant or lactating women; and9.those who participated in other clinical studies within 30 days prior to the screening for this clinical study.

### Recruitment, randomization, blinding and non-blinding

3.6

Advertisements for patient recruitment will be posted on the Catholic Kwandong University International St. Mary's Hospital bulletin boards, along with posters, banner advertisements and internet cafes. All advertisements will be run after IRB approval.

Individuals who have given written consent for participating in the study will be assigned a screening number, in order of the outpatient visit at screening. Unblinded sub-investigators, who do not influence the research results and analysis, will refer to the randomization list that has been prepared by a commissioned professional statistician, and assign participation numbers by stratification (based on the presence of breast cancer or colorectal cancer). The randomized list will be generated by layer considering the stratification factor by the block randomization method, and participants will be allocated to the pregabalin group, the pregabalin + EA group, and the pregabalin + CMT group in a ratio of 1: 1: 1. A randomization table is generated by an independent statistician and patients are assigned to one of three groups according to the randomization table. Screening numbers, randomization numbers, and initials assigned to each participant are used as subject identification codes to identify the participant until the end of the clinical trial.

The pregabalin used in this study is not a clinical investigational product and does not require allocation concealment, since it is administered to all groups. Moreover, it is impossible to blind the investigator and the participant in each group due to the nature of the study intervention, which is based on the contact between the patient and the medical staff. Instead, the investigator maintains blinding to prevent bias in evaluating the participant. If the clinical trial is completed, all clinical report forms (CRFs) are collected, the database process is terminated, and unblinding will be performed, if required for statistical analysis. Moreover, if it is deemed necessary to confirm the subject group due to an emergency situation during the clinical trial, the randomization code will be disclosed only to the participant, according to the principal investigator's discretion. If it is not possible to consult with the principal investigator and the situation is urgent, the randomization code of the subject will be disclosed after consultation with the randomization code officer. If unblinding is performed, the documentation of the reason for the unblinding will be retained and the participant with the disclosed randomization code will not be able to continue the trial.

